#### 2.2.1. Follow-up period

The follow-up period for each patient will be 12 months, with 5 scheduled visits (initial, after 1, 3, 6, and 12 months).

#### 2.2.2. Data collection and management

Measurements will be obtained as follows: (1) Pre-intervention: Initial or baseline data collection; (2) Intervention: Data will be collected at 1, 3, and 6 months after the baseline visit; (3) Postintervention: twelve months after recruitment, the patient will be interviewed to assess whether he/she maintains his/her status regarding the change of behavior over time.

The data obtained will be recorded in the data collection notebooks and sent online to the study coordinator for further processing, cleaning, and statistical analysis.

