**Materials and methods:**

A cluster-randomized, two-arm parallel, multicenter, open-label, controlled clinical trial. Fifty PC healthcare professionals from the province of Córdoba (Spain) will be randomized to one of the two study groups: (1) Experimental Group (EG): MI-based approach; (2) Control Group (CG): Usual care based on health advice. EG intervention: Professionals will receive a training program focused on MI, consisting of a training workshop and the use of pre- and post-workshop questionnaires to measure knowledge and skills acquired, as well as the degree of empathy, with a videotape of the health professionals with standardized patients, before and after the workshop, and subsequent training feedback. CG intervention: Workshop on the management of risky alcohol use based on health advice; participants will also complete the pre-and post-workshop questionnaires and be videotaped. Study population: Patients ≥ 14 years old with risky alcohol consumption (28 Standard Drink Units-SDU-/week in men and 17 SDU/week in women) or excessive alcohol use (≥ 6 SDU in men or ≥ 4 SDU in women, in less than 2 h). It would be necessary to include 110 subjects/group to find a difference of 20% between the percentage of patients in abstinence between EG (37%) and CG (20%), alpha error of 5%, and statistical power of 80%. Assuming a loss rate of 5% and the cluster design effect, the number of subjects to be recruited is estimated at 197/group. The follow-up period will be 12 months. The primary outcome variables will be the self-reported alcohol use level and the Alcohol Use Disorders Identification Test (AUDIT) questionnaire score.

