## 2. Methods and analysis

### 2.1. Study design

This is a cluster-randomized, two-arm parallel, multicenter, open-label, controlled clinical trial that will be conducted in PC centers of the Andalusian Health Service located in the province of Córdoba (Spain). PC professionals will be randomized to one of two study groups (Figure 1): (1) Experimental Group (EG): Professionals will implement an approach based on brief motivational intervention (18) applied on patients with risky alcohol use, receiving previously a specific training program in this field; (2) Control Group (CG): Professionals will also receive prior training on the management of the patient with risky alcohol consumption and will implement the usual clinical care (health advice) in recruited patients. Participants in both groups will attend a workshop focused on the identification and management of patients with risky alcohol consumption.

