### 2.3. Statistical analysis

An intention-to-treat analysis will be performed to control the effects of losses and dropouts, dragging for analysis the data from the last observation obtained. Survey data will be automatically processed on Google Drive, directly by each of the participating researchers. They will then be exported to an Excel sheet from Google Drive and statistically treated with the SPSS v. 17.0. A descriptive analysis and an initial comparability analysis of the groups will be conducted. Confidence intervals of 95% will be calculated for the major study estimators. A bivariate analysis will be conducted to assess the relationship of the independent variables and the effect of the intervention, for which the Chi-square test will be used, the mean comparison test for independent samples, such as Student *t* test or ANOVA (after verification of normality by using the Kolmogorov-Smirnov test); bilateral comparisons were used, and a value of *p* ≤ 0.05 will be considered. A multivariate analysis will then be performed to determine which sociodemographic, work, and care factors are associated with the intervention developed, controlling the predictors and/or confounders by multiple linear regression and unconditioned binary logistic regression.

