**-Variables measured in patients with risky alcohol use:**

To assess the effectiveness of interventions, the main outcome variables will be the number of SDU in a typical day, the frequency of more than 6 SDU/day, and the total score of the AUDIT (21) questionnaire. All these variables will be considered as primary outcomes.

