#### 3.1.2. Limitations

It is necessary to keep in mind and recognize the possible bias known as the Hawthorne effect (observer bias) (31), which is inevitable or difficult to minimize in this type of experimental study, in which subjects usually change their behavior by the fact that they feel observed. If there is a high rate of professional or patient dropouts, withdrawals, or losses, the selection bias may become so important that can alter the actual results. Biases of information may occur due to the possible lack of sincerity of the respondent in answering questions regarding knowledge and attitudes regarding their alcohol consumption. Confusion biases will be controlled by multivariate analysis.

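### The 12-month measurement is taken by interview in an open-label trial with self-reported patient primary outcomes, and no assessor separate from the treating professional is described; private self-completion would be a low-cost safeguard.

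*Protocol article*

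**What the plan says.** - **Design.** Section 2.1: "This is a cluster-randomized, two-arm parallel, multicenter, open-label, controlled clinical trial". The same section has the randomized professionals deliver the allocated approach, and section 2.1.1.1 has each of them recruit 7–8 patients.
- **Patient primary outcomes.** Section 2.5.1: "the main outcome variables will be the number of SDU in a typical day, the frequency of more than 6 SDU/day, and the total score". Each of the three counts as primary, and the score meant is the one from the AUDIT. The abstract describes them this way: "The primary outcome variables will be the self-reported alcohol use level and the Alcohol Use Disorders Identification Test (AUDIT) questionnaire score". Table 1 lists no objective marker of drinking.
- **How measurements are obtained.** Section 2.2.2 sets this out by phase. During the intervention phase, "Data will be collected at 1, 3, and 6 months after the baseline visit", with no mode given. At twelve months, "the patient will be interviewed to assess whether he/she maintains his/her status regarding the change of behavior over time". Results are entered in data collection notebooks and sent online to the coordinator.
- **Data handling.** Section 2.3: "Survey data will be automatically processed on Google Drive, directly by each of the participating researchers". Patients lost to follow-up have their last observation carried forward.
- **Acknowledged hazard.** Section 3.1.2: "Biases of information may occur due to the possible lack of sincerity of the respondent". The next sentence assigns multivariate analysis to confounding. Nothing is set against insincere answers.

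**The concern.** Neither patient nor professional is blinded, and the outcome is what the patient says about drinking. If that is said face to face to someone who knows the allocation, the wish to give a good answer, and the way it is recorded, can both depend on arm.

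The arms differ in a way that makes this plausible. Experimental professionals are trained in the skills listed under the EVEM scale in section 2.2, among them empathy, validating the patient and agreeing objectives for change. Control professionals give their usual informative and persuasive advice (section 2.1.4). A patient who has agreed a goal with a clinician has a particular reason to report having met it. The expected direction favours the intervention.

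Misreporting that is equal in both arms mostly blurs the comparison. Misreporting that differs by arm shifts the estimate, and adjusting for measured covariates does not remove it, because the error lies in the outcome itself and moves with allocation. All three patient primary outcomes are exposed.

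**Working it through.** **1. The plan's own sample size (section 2.4).** Inputs: 37% v 20%, two-sided alpha 5%, power 80%.

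n = [1.960·√(2·0.285·0.715) + 0.842·√(0.37·0.63 + 0.20·0.80)]² / 0.17² = 109.5, so 110 per group.

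Design effect: 1 + (15 − 1)·0.05 = 1.70. Then 110·1.70 = 187, and 187/0.95 = 196.8, so 197 per group. Both stated figures are reproduced.

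**2. Effective size per arm.** Starting from 197 and removing 5% for losses:
- with the protocol's design effect of 1.7: 197·0.95/1.7 = 110;
- with the planned cluster size, 394 patients over 50 professionals = 7.88 each: 1 + 6.88·0.05 = 1.344, and 197·0.95/1.344 = 139.

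**3. False-positive rate under differential reporting.** Assumptions, none of them from the documents: no true effect, true success 20% in both arms, and an excess b of falsely reported success in the experimental arm only. With p₁ = 0.20 + b, p₂ = 0.20 and p̄ their mean:

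- s₀ = √(2·p̄(1 − p̄)/n)
- s₁ = √((p₁(1 − p₁) + p₂(1 − p₂))/n)
- rejection probability = Φ((b − 1.96·s₀)/s₁) + Φ((−b − 1.96·s₀)/s₁)

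For b = 0.05 and n = 110: s₀ = 0.0563, s₁ = 0.0562, giving Φ(−1.07) + Φ(−2.85) = 0.1415 + 0.0022 = 0.144.

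| Assumed excess | n = 110 (design effect 1.7) | n = 139 (design effect 1.344) |
|---|---|---|
| 0 points | 5.0% | 5.0% |
| 3 points | 8.4% | 9.3% |
| 5 points | 14.4% | 16.9% |
| 8 points | 28.4% | 34.5% |

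Almost all rejections favour the experimental arm (14.2 of the 14.4 percentage points in the worked case). An excess of 5 points is 5/17 = 29% of the difference the trial is sized to detect. The effective sizes presume an analysis that respects clustering.

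**4. What the arithmetic does not show.** It uses the binary abstinence endpoint of section 2.4, not the three primary outcomes of section 2.5.1. It shows that bias of this size would matter. It does not show that such bias will occur, or how much of it a change of mode would remove.

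**The case against.** The strongest reply is that the text does not say what a reader may infer from it.

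- **Who interviews.** A reader might conclude that the treating professional takes the primary outcomes at every visit. The article does not say so. The interviewer is not named, and that it is the treating professional is an inference from the roles in sections 2.1 and 2.1.1.1.
- **Which items and visits.** Interview is stated only for twelve months, with the purpose of seeing whether a change has been maintained. No mode of administration for AUDIT or the drinking items is given at any visit, so self-completion is not excluded.
- **Google Drive.** The sentence on survey data does not prove that professionals handle patient drinking data. The term is undefined, and professionals fill in questionnaires too.
- **Benefit of the remedy.** A reader might claim that self-completion would remove most of the bias at almost no cost. Nothing in the document supports that.
- **Size.** The bias values are assumed, and the design effect of 1.344 is not the protocol's. Removing 5% for losses also sits beside a plan to carry the last observation forward.
- **Context.** A condensed article may leave operational detail to the full protocol. Section 3.1.2 already discloses the risk, and a real-conditions trial can be expected to be open-label.

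Most of this stands, and it limits the point to what is claimed here. It does not dispose of it. Section 2.2.2 sets out how measurements are obtained and names an interview for the final one, which is a stated method and not merely a missing detail. Disclosing a bias is not a safeguard against it. The size is therefore shown under the protocol's own design effect as well.

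**Conclusion.** The point holds in limited form. An open-label trial with self-reported patient primary outcomes takes its twelve-month measurement by interview. The professionals who were randomized recruit and treat the patients, no separate assessor is described, and insincere answering is acknowledged without a safeguard. The planned adjustment for confounding cannot repair misreporting that differs by arm.

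The size is illustrative. A 5-point excess of false success would lift a 5% error rate to about 14% (design effect 1.7) or 17% (1.344), resting on the assumptions in step 3 of the working. The share that private completion would prevent cannot be calculated from the document. It may reduce differential reporting but will not eliminate it.

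**What to change.** In section 2.2.2, state that at every follow-up visit where they are collected the patient completes the research drinking items privately, on paper or online, before seeing the professional. By Table 1 that means SDU at 1, 3, 6 and 12 months and AUDIT at 3, 6 and 12 months. The frequency of more than 6 SDU/day has no row of its own in Table 1 and should be taken the same way whenever it is collected.

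State also that these research answers go directly to the coordinator and are not shown to the treating professional, and that the interview is kept for clinical follow-up. Use one mode at all follow-up visits. If only the twelve-month visit changed, values carried forward from earlier visits could have been collected differently from those they are compared with.

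If a fuller protocol already provides for this, one sentence in the article is enough. Otherwise the cost is low: protocol wording and a patient-facing form, with no extra interviewer. The downside is some missing items and some patients who need help with reading, for which a helper other than the treating professional should be named.

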### 2.3. Statistical analysis

An intention-to-treat analysis will be performed to control the effects of losses and dropouts, dragging for analysis the data from the last observation obtained. Survey data will be automatically processed on Google Drive, directly by each of the participating researchers. They will then be exported to an Excel sheet from Google Drive and statistically treated with the SPSS v. 17.0. A descriptive analysis and an initial comparability analysis of the groups will be conducted. Confidence intervals of 95% will be calculated for the major study estimators. A bivariate analysis will be conducted to assess the relationship of the independent variables and the effect of the intervention, for which the Chi-square test will be used, the mean comparison test for independent samples, such as Student *t* test or ANOVA (after verification of normality by using the Kolmogorov-Smirnov test); bilateral comparisons were used, and a value of *p* ≤ 0.05 will be considered. A multivariate analysis will then be performed to determine which sociodemographic, work, and care factors are associated with the intervention developed, controlling the predictors and/or confounders by multiple linear regression and unconditioned binary logistic regression.

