### 2.4. Sample size

Based on a previous study performed by our team members (26), and to find a 20% difference between the percentage of patients in abstinence (partial or total) between EG (37%) and CG (20%), for an alpha error of 5%, and statistical power of 80%, the size would be 220 subjects (110/group). Since it is a cluster randomization system, we will consider the “design effect” and we will assume a loss rate of 5%. Estimates of the intra-cluster correlation coefficient (ICC) in ECC by clusters in PC show that they are generally less than 0.05 (27). This ICC translates, for a cluster size of 15, into a design effect corresponding to a factor of 1.7. Assuming this value, the size would be 394 subjects to recruit (197 in each group).

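### Last observation carried forward is the only stated handling of lost patients: it assumes the maintenance that the 12-month visit is meant to assess, and it can bias the result either way

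*Protocol article*

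**What the plan says.** Section 2.3 of the protocol article states: "An intention-to-treat analysis will be performed to control the effects of losses and dropouts", and gives the means as "dragging for analysis the data from the last observation obtained". That is LOCF. The section names no other missing-data method, and the tests it lists (chi-square, t test or ANOVA, ordinary linear and logistic regression) make no distinction between carried and measured values.

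Four other places bear on this:

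- Section 2.2.2 treats months 1, 3 and 6 as the intervention period. At twelve months, post-intervention, "the patient will be interviewed to assess whether he/she maintains his/her status regarding the change of behavior over time".
- Section 2.5.1 says of the patients that "the main outcome variables will be the number of SDU in a typical day, the frequency of more than 6 SDU/day", together with the total AUDIT score; all three are primary.
- Table 1 schedules SDU at all five visits, but AUDIT only at baseline and months 3, 6 and 12.
- Section 2.4 says "we will assume a loss rate of 5" per cent, while section 3.1.2 concedes: "If there is a high rate of professional or patient dropouts, withdrawals, or losses, the selection bias may become so important" as to change the results.

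**The concern.** LOCF supplies an answer where the trial is asking a question. The 12-month visit is meant to show whether a change in drinking lasts. For anyone lost after month 1, 3 or 6, the rule takes it as given that it did. These are the patients about whom least is known.

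The rule also treats the primary outcomes unevenly, because they do not share a visit schedule. The carried values are then tested as though they had been measured at the end of follow-up.

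At stake is the claim that the rule controls the effect of losses. It does not. It replaces one unknown with a fixed assumption, and the resulting error depends on when patients leave, how many leave, and whether the arms differ in either respect.

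**Working it through.** **Step 1. The plan's own figures.** Inputs from section 2.4: 37% against 20%, power 80%, ICC 0.05, cluster size 15, loss 5%. Alpha is 5%, two-sided by section 2.3. The article calls the difference 20%, but 37 − 20 = 17 points, and 17 is used here.

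- Mean proportion 0.285. n = [1.96·√(2·0.285·0.715) + 0.842·√(0.37·0.63 + 0.20·0.80)]² / 0.17² ≈ 109.5, so 110 per group. Reproduced.
- Design effect 1 + (15 − 1)·0.05 = 1.7. Then 110·1.7 = 187, and 187/0.95 = 196.8, so 197 per group. Reproduced.
- Planned loss is 197·0.05 ≈ 10 patients per group. LOCF does not enter this calculation. Without it, 197·0.95/1.7 ≈ 110 effective patients per group still give 80.2% power.

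**Step 2. What is carried, from Table 1.**

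| Last visit attended | SDU carried from | AUDIT carried from |
|---|---|---|
| Baseline | Baseline | Baseline |
| Month 1 | Month 1 | Baseline |
| Month 3 | Month 3 | Month 3 |
| Month 6 | Month 6 | Month 6 |

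In the second row, two primary outcomes of the same patient refer to different sides of the start of the intervention.

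**Step 3. Size and direction of the bias.** In each arm let d be the fraction lost, c the success rate carried forward for them and t their true 12-month rate. Then

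bias in the difference = d_EG·(c_EG − t_EG) − d_CG·(c_CG − t_CG).

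The documents give no c or t, so the rows below are assumptions.

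| Assumption about lost patients | Loss EG / CG | Bias, points |
|---|---|---|
| 17-point gap carried from month 3, true gap 0 | 5% / 5% | 0.05·17 = +0.85 |
| Same | 20% / 20% | 0.20·17 = +3.4 |
| Lost before month 1, counted as failures, true gap 17 | 5% / 5% | 16.15 − 17 = −0.85 |
| Same | 20% / 20% | 13.6 − 17 = −3.4 |
| Carried rate 15 points too high in both arms | 15% / 5% | 0.15·15 − 0.05·15 = +1.5 |
| Same | 5% / 15% | 0.05·15 − 0.15·15 = −1.5 |
| True 10% in both arms; carried 45% EG, 25% CG | 30% / 15% | 0.30·35 − 0.15·15 = +8.25 |

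**Step 4. Effect on the test.** A simulation used a standardised continuous outcome, 197 per arm, 4,000 runs, an assumed between-visit correlation of 0.6 and no clustering. Losses were random and spread evenly over the four possible last visits. The arms were equal at month 12, but EG was assumed to be ahead by 0.3, 0.3 and 0.2 SD at months 1, 3 and 6. The expected shift is d times the mean of (0, 0.3, 0.3, 0.2), or 0.2·d, in favour of EG.

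| Loss per arm | Expected shift, SD | Simulated shift, SD | Rejection, LOCF | Rejection, completers |
|---|---|---|---|---|
| 5% | 0.010 | 0.010 | 5.2% | 5.1% |
| 20% | 0.040 | 0.041 | 7.2% | 5.4% |
| 30% | 0.060 | 0.058 | 9.2% | 5.0% |

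With the same time course in both arms, LOCF rejected 5.0% of the time at 5% loss and 4.8% at 20%.

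**Step 5. Precision.** Counting carried values as observed makes the standard error √(1 − d) of the one based only on patients measured at month 12: 0.975 at 5% loss and 0.894 at 20%, so 2.5% and 10.6% smaller.

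**The case against.** The strongest reply is that little would change as the trial is planned. At 5% loss about 95% of patients are measured at month 12, so maintenance is still tested in nearly everyone. The bias is under one point in the fading scenario and the rejection rate is practically nominal. The article also names no primary time point; month 12 is inferred from sections 2.2.1 and 2.2.2. The 17 points describe abstinence, which is not among the listed patient primary outcomes, and no bias can be computed from the documents on the SDU or AUDIT scale. Finally, a mixed model has its own untestable assumption, missing at random. All of this stands and limits the size of the point. It does not rescue the rule, which is fixed in the current text and is not a detail left for later.

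Three stronger readings are tempting but unsupported:

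- A reader might infer that LOCF must favour the motivational arm. Step 3 shows equal and opposite errors, and the month-1 AUDIT case itself carries a pre-intervention value, which dilutes an effect.
- A reader might take the planned minimum of 20 final-year residents among 50 professionals (section 2.1.2), which is 40%, as a likely loss rate. That is a staffing share. Nothing says that residents will leave or that their patients will be lost.
- A reader might infer that LOCF by itself inflates the false-positive rate through too small a standard error. In the simulation the calculated standard error (about 0.101) matched the actual spread of the estimates (about 0.102) at 20% loss. The excess rejection came from the shift in the estimate, and only when the time courses differed. Precision is overstated only in the sense of Step 5.

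**Conclusion.** The point holds in a limited form. LOCF is a poor choice as the sole stated method: it assumes maintenance for lost patients in a trial that sets out to assess maintenance, and under Table 1 it mixes time points across primary outcomes. Its bias has no fixed sign.

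At the planned 5% loss the impact is small, up to about 0.9 points on the 17-point abstinence difference, assuming that the effect has fully faded and that dropouts were last seen at month 3. On the same assumptions it reaches 3.4 points at 20% loss, and loss that differs between arms can produce bias even where equal loss would not. The documents do not project loss above 5%, although section 3.1.2 admits the possibility of a high rate. The change should be made, because it is cheap and protects against that possibility, but as planned the rule does not threaten the trial's main conclusion.

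**What to change.** In section 2.3, replace LOCF as follows:

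- **Main analysis.** For each patient primary outcome (SDU in a typical day, frequency of more than 6 SDU/day, AUDIT score), fit a likelihood-based mixed model suited to its scale on all observed visits: SDU at months 1, 3, 6 and 12, AUDIT at months 3, 6 and 12. Table 1 gives the frequency outcome no row of its own, so state its visits. Include baseline, arm by visit, and random effects for patient and professional, and report the 12-month contrast. State how patients with no post-baseline value stay in the intention-to-treat analysis.
- **Binary abstinence, if analysed.** Use the corresponding mixed model, or multiple imputation that respects clustering by professional.
- **Sensitivity analyses.** Add delta-adjusted missing-not-at-random analyses for all outcomes, allowing different deltas by arm, and for abstinence an analysis that counts missing as not abstinent. Keep LOCF at most here.

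The cost is slightly more programming, a check that the named software fits these models, and reliance on missing at random in the main analysis, which the delta analyses are there to probe. The visits are already scheduled, so no extra data are needed, and 197 per group stands as far as this change is concerned.

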#### 2.1.3. Random assignment

The randomization unit will be the healthcare professional, and the intervention unit will be the patient. Professionals will be randomly assigned and equally (1:1) to one of the two study groups (EG or CG), stratifying according to the center and type of professional. Patients will be recruited through consecutive sampling (opportunistic search of subjects who are treated at participating health centers).

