### 2.2. Materials and methods

Participants’ information will be obtained from validated tools for assessing risky alcohol use (AUDIT) (21) and the motivational interview (EVEM questionnaire) (22). In addition, the Jefferson (23) scale will be used to assess the empathy of healthcare providers in the management of alcohol use.

-AUDIT (21). Tool designed to identify risky alcohol use that comprises 10 questions divided into 3 conceptual domains. The first domain evaluates recent alcohol consumption and contains three questions (frequency of alcohol use, usual amount of alcohol consumption, and frequency of binge drinking). The second domain assesses symptoms of dependence through three items (loss of control over consumption, increased relevance of consumption and morning drinking). The third domain assesses harmful alcohol use through four questions (feeling of guilt after drinking, memory gaps, alcoholrelated injuries and concerns about drinking). A result equal to or above eight is considered indicative of hazardous and harmful consumption, and a possible alcohol dependence.

-Scale for the assessment of the MI (EVEM) (22). A scale of 14 items with a score of 0 to 4, created to assess encounters between professionals and patients using MI. This scale analyzes: (1) empathy; (2) facilitating patient positioning; (3) working in concordance with the patient; (4) using open questions; (5) performing reflective listening; (6) performing summaries; (7) validating the patient; (8) agreeing on change objectives; (9) promoting action/plan design with the patient; (10) Prevents discord with patient; Global Interview Spirit: (11) evokes; (12) collaborates; (13) honors patient autonomy; (14) shows compassion. This scale has been validated by members of this group (24).

-Empathy Scale (Jefferson Scale) (23), which evaluates three dimensions of empathy: Taking perspective, caring with compassion, and standing in the patient’s shoes. It consists of 20 Likert-type questions with a 7-point response range from strongly disagree (score = 1) to strongly agree (score = 7).

-Knowledge and Attitude Questionnaire: Based on the questionnaire created by our team for a previous study (25), and which was subjected to a process of apparent or consensus logical validity and content validity.

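### No rank or ordinal method is listed for the primary outcome on frequency of heavy drinking; if it is recorded in a few levels, unordered chi-square is the only listed two-group test left

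*Protocol article*

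**What the plan says.** Section 2.5.1 names three patient outcomes and declares all of them primary. One is "the frequency of more than 6 SDU/day"; the others are the number of standard drink units (SDU) on a typical day and the total AUDIT score. Section 2.2 describes the first AUDIT domain as "frequency of alcohol use, usual amount of alcohol consumption, and frequency of binge drinking", so a question of this kind sits inside the questionnaire. Neither section gives the answer format or the coding.

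Section 2.3 lists the methods as one pool. The bivariate analysis covers "the effect of the intervention, for which the Chi-square test will be used", followed by a comparison of means (Student t test or ANOVA) once normality has been verified by Kolmogorov-Smirnov. It adds that "bilateral comparisons were used". The multivariate analysis proceeds "by multiple linear regression and unconditioned binary logistic regression". No method is tied to a named outcome, none is rank-based or ordinal, and nothing is said about what happens if the normality check fails.

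**The concern.** The effect the trial looks for is a general shift towards less frequent heavy drinking. Unordered chi-square ignores the order of the levels and spreads its sensitivity over every pattern of difference, using one degree of freedom for each level beyond the first. It is therefore weak against a shift in one direction. Binary logistic regression reduces the outcome to a yes/no at a cut point, and none is given for this outcome. A cut chosen after the data are seen adds a free choice to a primary outcome of an open-label trial.

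A mean comparison on level codes would keep nearly all the power, but the plan's own condition shuts it out if the outcome has only a few levels. At stake is a real effect on a primary outcome being missed with data the trial already holds.

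**Working it through.** **1. The plan's own figure.** Section 2.4 sizes the trial on a different, binary endpoint: abstinence of 37% against 20%, alpha 5%, power 80%, two-sided.

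n = [1.960 × √(2 × 0.285 × 0.715) + 0.842 × √(0.37 × 0.63 + 0.20 × 0.80)]² / 0.17² = (1.251 + 0.528)² / 0.0289 ≈ 109.5, so 110 per group.

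Design effect 1 + (15 − 1) × 0.05 = 1.7; 110 × 1.7 = 187; 187 / 0.95 = 196.8, so 197 per group and 394 in all. The stated size reproduces. The article gives no power for the frequency outcome, so there is no figure of its own to check there.

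**2. Effective sample size per arm.** 197 × 0.95 ≈ 187 patients analysed.
- No clustering: 187.
- Section 2.1.1.1 has each professional recruit 7–8 patients. With 7.5 and the article's ICC of 0.05, the design effect is 1 + 6.5 × 0.05 = 1.325, and 187 / 1.325 ≈ 141.
- The article's own design effect of 1.7: 187 / 1.7 = 110.

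**3. Does the normality condition shut out the t test?** If an item has k levels, at least one holds a share of 1/k or more. The empirical distribution jumps by that share, so its largest distance from any continuous curve is at least half the jump. With five levels the distance is at least 0.10, with four 0.125, with three 0.167. The 5% Kolmogorov-Smirnov limit at 187 patients is about 1.358 / √187 = 0.099. An item with up to five levels therefore fails whatever its distribution. Simulation agrees: normality was rejected in every draw for items with three, four and five levels at 187 per arm, with and without the Lilliefors correction, and in every draw for the skewed counts tried.

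**4. Power under assumed inputs.** The number of levels, their distribution and the effect are not in the documents. Assumed: three to five levels, proportional odds, and control distributions from uniform to skewed. Two odds ratios were used: 1.8 (assumed) and 2.35, which is the article's abstinence contrast, (0.37/0.63) / (0.20/0.80), applied to every cut. The comparator is the tie-corrected Wilcoxon test, which stands in for the proportional-odds test.

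| Effective n per arm | Odds ratio | Levels | Ordinal test | Unordered chi-square | Loss (points) |
|---|---|---|---|---|---|
| 141 | 1.8 | 5 | 76–79% | 55–58% | 20–22 |
| 141 | 1.8 | 4 | 76–78% | 60–63% | about 16 |
| 141 | 1.8 | 3 | 76% | 65% | about 11 |
| 110 | 2.35 | 5 | 91–95% | 77–82% | 12–15 |
| 187 | 2.35 | 5 | 99% or more | 96–97% | 2–4 |

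Over three to five levels and 110 to 187 effective patients, the loss runs from about 8 to about 22 points at an odds ratio of 1.8. At 2.35 it runs from about 1 point (three levels, 187) to about 17 points (five levels, 110, half the control patients in the lowest level: about 89% against 72%). With no effect, both tests rejected in about 5% of runs.

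**5. The other listed routes.** With five levels, 110 per arm and the effect set so that the ordinal test has about 80% power:
- dichotomising at the best cut loses 6–13 points, and at a poor cut up to 66;
- a t test on level codes loses only 0–3 points.

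**The case against.** A reader might infer that the plan prescribes chi-square and binary logistic regression for this outcome and so gives up a fixed 10 to 21 points of power. The documents do not support that. Section 2.3 assigns no method to any named outcome. Multiple linear regression is listed without the normality condition and, applied to level codes, would keep most of the power. Nor does the section say that a failed normality check sends an outcome to chi-square.

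The answer format is not given either. The outcome could be a count of days, and the figures above would then not apply. The size of the loss depends on assumed levels, distribution and effect, and at 2.35 with little clustering it nearly vanishes.

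The calculation also uses effective sample sizes, whereas Section 2.3 names no clustering adjustment. The table therefore compares tests that both allow for clustering; it does not give the power of the chi-square as written. Finally, a journal article may leave the model for each outcome to a fuller plan.

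All of this limits the claim; it does not remove it. The article goes beyond silence: it states a list of methods, and that list contains nothing made for ordered data and no fallback if normality fails. Linear regression is not assigned to this outcome, and the multivariate step is described as a search for associated factors with control of confounders. By the article's own condition, chi-square remains the only listed two-group test for a few-level item.

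**Conclusion.** The point stands in conditional form. The outcome is primary and ordered, Section 2.3 lists no rank or ordinal method, and its normality condition would exclude the mean comparison for a few-level item or a skewed count. If unordered chi-square is then used, the loss is about 8 to 22 points of power at an odds ratio of 1.8 and about 1 to 17 points at 2.35. This rests on three to five levels, proportional odds, 110 to 187 effective patients per arm and the distributions tried. It is a range under stated assumptions, not a property of this trial. The stated sample size is unaffected, since it was computed for another endpoint. This is a worthwhile correction to a primary analysis, not a defect that would invalidate the trial.

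**What to change.** In Section 2.3, state how this outcome is recorded and name its analysis:
- a proportional-odds model if it is recorded in ordered levels, or a rank-based test if it is recorded as a count;
- adjustment for the baseline value of the outcome;
- an explicit allowance for clustering by professional, for example a random effect or cluster-robust standard errors. It has to be written out, because Section 2.3 contains none to refer to, while under Section 2.1.3 "Professionals will be randomly assigned and equally (1:1) to one of the two study groups";
- the common odds ratio with its 95% confidence interval as the reported effect, where the proportional-odds model is used.

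Keep the chi-square table as description only. The cost is a sentence or two, fixed before outcome data are compared by arm, and no new data. The small downside is that the common-odds assumption has to be checked.
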